#### Process Evaluation

Analysis to assess the fidelity of the intervention will be undertaken. Specifically, 50-100 random patient charts from the 3 sites (HHS, St. Joseph’s Healthcare Hamilton, NHS) will be reviewed to assess discharge prescription duration and compare findings against ODB data to assess the level of agreement between the length of the discharge prescription and pharmacy dispensation. In this sample population, we will assess the proportion of patients who received a prolonged duration discharge prescription as reported in hospital charts compared to the proportion who received a prolonged duration discharge prescription in the ODB record. Selection of participant charts for evaluation will be identified from local (HHS, NHS) access to CorHealth registries. These local registries are available for hospital use for approved research and quality assurance work.

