### Rationale and Study Objectives

Poor medication adherence was identified by the World Health Organization in 2003 as a worldwide challenge in the management of chronic diseases [17]. The consequences of suboptimal adherence include undesirable health outcomes as well as increased health care costs. Both provider-level and system-level factors play important roles in optimizing adherence. We have previously shown that inappropriate beliefs regarding risk perception and outcome expectancies, prescription refill burden, and unintentional forgetfulness due to lack of habituation all contribute to the observed general decline in medication adherence over time [18-20]. Providing longer prescriptions at the time of discharge can address all of these barriers. However, prescriptions covering ≥90 days are currently provided to only 21% of all cardiac patients and to no more than 54% of MI patients, suggesting an opportunity for this change to benefit many patients [4,21].

We know of no guidelines or practice standards for physicians that recommend the prescription of maximum duration (ie, ≥90 days) for cardiac medications at discharge. The use of standardized hospital-based medication discharge practices has been shown to minimize medication errors and to optimize guideline-recommended therapies [22]. However, no prospective study has evaluated the effects of implementing an institutional policy or standardized discharge cardiac medication prescriptions of maximum duration on long-term medication adherence. Therefore, it is hypothesized that longer prescription duration at discharge will promote better long-term cardiac medication adherence.

The specific objectives of this study include estimating and comparing the effects on long-term cardiac medication adherence of (1) a standardized discharge form featuring prescription duration of 90 days with 3 repeats in post-MI patients in combination with education, (2) education only, and (3) usual care (ie, no intervention regarding prescription duration) and assessing the economic implications of the prolonged initial discharge prescriptions as compared to usual care. To our knowledge, this project is the first interventional study to investigate how modifying prescription duration impacts medication adherence.

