#### Secondary Outcomes

Class-specific adherence (defined as a dichotomous outcome) will also be independently defined as PDC ≥80% for a given drug class at 1 year from discharge. Class-specific medication persistence (defined as a dichotomous outcome) will also be independently defined as having claims for any type of medication within that class from discharge date through the following 365 days with no period of 30 days or more without supply (ie, a discontinuation). The number of unique cardiac medication classes (range, 1-4) filled by a patient at their index fill will also be modelled to investigate whether either intervention meaningfully altered the number of medication classes per patient. Additionally, at the time of a patient’s index fill, we will measure the number of days supplied per medication class and the average number of days supplied across all unique medication classes — both outcomes will be dichotomized (ie, ≥90 days supplied versus <90 days supplied).

In addition to medication adherence–based and persistence-based outcomes, we will assess health care utilization and adverse clinical outcomes at 365 days from discharge including the frequency of outpatient primary care visits, frequency of outpatient cardiology visits, hospitalization for cardiovascular disease, hospitalization due to repeat acute MI, hospitalization due to stroke, repeat cardiac catheterization, coronary revascularization, and death. For both visit-based outcomes, visits occurring on the same day as discharge will be excluded.

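### The chart review aims at agreement between prescribed and dispensed length, but the only measure it names compares two overall proportions, which bound patient-level agreement without determining it

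*Protocol article*

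**What the plan says.** The Process Evaluation section of the protocol article plans a fidelity check on "50-100 random patient charts from the 3 sites". The chart findings are to be set against ODB data "to assess the level of agreement between the length of the discharge prescription and pharmacy dispensation".

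The next sentence gives the measure. The share of patients with a long prescription is to be taken "as reported in hospital charts compared to the proportion who received a prolonged duration discharge prescription in the ODB record". According to Data Sources, ODB records dispensations, so the second proportion describes what was dispensed. Both proportions refer to the same sampled patients. The section names no cross-classification, percent agreement or other per-patient measure.

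Three other places bear on the point:
- Secondary Outcomes measures days supplied at the index fill for study patients generally, split as "≥90 days supplied versus <90 days supplied".
- Standardized Discharge Prescription Forms describes monthly ward visits in intervention group 1 to check that the form was in use.
- Rationale and Study Objectives gives a background level: "prescriptions covering ≥90 days are currently provided to only 21% of all cardiac patients and to no more than 54% of MI patients".

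**The concern.** The aim is a question about individual patients: was the length written on this patient's prescription the length the pharmacy dispensed? The named measure answers a different question, namely whether the two sources give the same overall percentage. Long prescriptions dispensed short and short prescriptions dispensed long cancel in that comparison, so equal percentages do not show agreement. Unequal percentages show only the net shortfall.

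The dispensing side is already covered by the days-supplied outcome. What the chart review adds is the link, patient by patient, between what was prescribed and what was dispensed. That link helps tell whether a short first fill began with the prescriber or at the pharmacy. A comparison of margins discards it.

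**Working it through.** **Inputs.** The article states no target, expected proportion or power for this check, so there is no figure to reproduce. The sample is 50-100 charts (Process Evaluation). For illustration I take 54%, the upper figure for MI patients in Rationale and Study Objectives. I assume that prolonged means at least 90 days, the cut-off in Secondary Outcomes, because Process Evaluation does not define it. The arithmetic does not depend on the cut-off.

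**Bounds.** Let p1 be the proportion prolonged by chart and p2 the proportion prolonged by ODB. Agreement then lies between |p1 + p2 - 1| and 1 - |p1 - p2|. With p1 = p2 = p, minimum agreement is |2p - 1| and maximum disagreement is 2 x min(p, 1 - p).

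**At p = 54%.** Minimum agreement is |2 x 0.54 - 1| = 0.08 and the maximum is 1.00. Agreement expected by chance is 0.54² + 0.46² = 0.2916 + 0.2116 = 0.5032. At the minimum, kappa = (0.08 - 0.5032) / (1 - 0.5032) = -0.85.

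Four tables for n = 100 all give 54% against 54%, a difference of 0:

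| Both long | Chart only | ODB only | Neither | Agreement | Kappa | Long prescriptions dispensed long |
|---|---|---|---|---|---|---|
| 54 | 0 | 0 | 46 | 100% | 1.00 | 54/54 = 100% |
| 29 | 25 | 25 | 21 | 50% | -0.01 | 29/54 = 54% |
| 20 | 34 | 34 | 12 | 32% | -0.37 | 20/54 = 37% |
| 8 | 46 | 46 | 0 | 8% | -0.85 | 8/54 = 15% |

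The second row is close to chance pairing. The named comparison cannot tell these rows apart; a per-patient measure does.

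**Other values of p, equal margins.** Maximum disagreement is 42% at p = 21%, 50% at 25%, 100% at 50%, 50% at 75% and 20% at 90%. A majority of patients can be discordant only when p lies strictly between 25% and 75%.

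**Unequal margins (assumed figures).** With 80% long by chart and 60% long by ODB, the difference is 20 points. The both-long cell can range from 0.80 + 0.60 - 1 = 40% to 60% of patients. The share of long prescriptions dispensed as long then ranges from 40/80 = 50% to 60/80 = 75%. Agreement ranges from 40% to 80%.

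**One-directional case.** If no short prescription is dispensed long, the ODB-only cell is 0. The difference p1 - p2 then equals the discordant share exactly, and the named comparison measures the shortfall correctly.

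**Precision.** If observed agreement were 80% (assumed), the Wilson 95% interval would be 67.0% to 88.8% with 50 charts and 71.1% to 86.7% with 100.

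**The case against.** The strongest reply is that the section does not call the two proportions the sole or deciding measure. Its wording about setting chart findings against ODB data allows a per-patient comparison, and a condensed article may leave the table to a fuller document. This stands in part: a per-patient analysis is not excluded. But the article does not simply omit the measure. It names one, and the one named does not answer the stated aim.

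A second reply is that the 8% figure needs 46 of 100 patients cut short and exactly 46 others dispensed more than was prescribed. The article describes a concern in one direction only, a trial dispensation shortening a 90-day prescription, and gives no mechanism for the reverse. This stands. The low end is a worst case, and one-directional shortening would be detected. The two proportions alone cannot confirm that discordance runs one way; the paired table shows it directly.

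Three stronger readings are tempting, and the article does not support them:
- A reader might infer that a null result could not be separated from a delivery failure at the pharmacy. The days-supplied outcome at the index fill would show low dispensing directly, in far more than 50-100 patients, and ward visits monitored use of the form in group 1.
- A reader might infer that the margins say nothing about agreement. They bound it on both sides, and unequal margins prove some disagreement.
- A reader might infer that equal proportions could always hide disagreement in most patients. That needs a prolonged share between 25% and 75%. At 21%, disagreement is capped at 42%. If the default form raised the share to 90%, the cap would be 20%.

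**Conclusion.** The point holds as a mismatch between aim and measure within Process Evaluation. Comparing the chart and ODB proportions shows the net difference. It bounds patient-level agreement but does not determine it: with both at 54%, agreement could be anywhere from 8% to 100%. That range rests on 54% as an illustrative value and on no restriction on the direction of discordance; under purely one-directional shortening the problem disappears. The loss is confined to patient-level agreement and to attributing short fills to the prescriber or the pharmacy. The primary outcome and its analysis are not affected. This is a minor, worthwhile improvement.

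**What to change.** Replace or supplement the comparison of proportions with a paired 2x2 table of prescribed at least 90 days by dispensed at least 90 days, applying the same cut-off to both sources. Report the share of long prescriptions dispensed as long with a 95% CI, and overall percent agreement with a 95% CI. Kappa and McNemar's test for the difference in margins are optional. Treat any split by intervention group or period as descriptive, because the sample is small.

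The cost is a little more analysis work and wide intervals. No extra charts are needed, provided chart and ODB records can be linked per patient, which the stated aim already presupposes.

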## Results

The primary outcome is long-term cardiac medication adherence assessed at 365 days from discharge. We calculated that 24 pre-intervention and 12 post-intervention intervals in each group will achieve 80% power to detect an immediate increase (intercept change) of 10% in the monthly proportion of patients with adherence (ie, proportion of days covered ≥80%) to their cardiac medication regimen at 1 year.

## Discussion

Based on previous observational studies [4,15,16], it is expected that long-term cardiac medication adherence among post-MI patients will improve following the implementation of a standardized discharge prescription length of 90 days with 3 repeats, in conjunction with educational outreach and support, as compared to usual care. Specifically, it is expected that the PDC will improve in each cardiac medication class. The PDC is considered a validated measure of medication adherence [38], and patients with a PDC ≥80% have been shown to have better clinical outcomes [34]. We do not expect that this intervention will increase the number of cardiac medications prescribed to post-MI patients at discharge; rather, we anticipate that standardized discharge prescription forms (in combination with education) will improve long-term adherence to the cardiac medications initiated at discharge.

Previous studies have demonstrated that a 10% increase in cardiac medication adherence in the setting of secondary prevention can result in a 6.7% relative reduction in major adverse cardiac events (MACE), including but not limited to death, MI, stroke, and revascularization procedures [38,39]. Assuming the 1-year MACE rate is 14.7% (based on a very large and high-quality RCT) [40] and estimating that there are approximately 3000 MIs in the study region in 1 year, we would expect the implementation of our intervention to prevent over 30 MACE per year and significantly reduce direct health care expenditures. This estimate only accounts for direct hospitalization costs and does not reflect other costs including rehabilitation, home care, and indirect community care costs. The cost implications of longer cardiac prescriptions at discharge are expected to be very minimal, with a surplus of medications likely administered in a minority of cases.

### Strengths

This study has several strengths. First, revised standardized discharge prescriptions forms are a low-cost and sustainable intervention. If this concept is demonstrated to be effective, the change to prescription duration could be easily implemented into existing discharge policies and even electronic medical records. Second, there is minimal risk associated with this intervention as the 5 discharge cardiac medications are all recommended for a minimum of 1 year post-MI and often lifelong. Cost limitations would be the only foreseeable risk, which are being evaluated as part of the health economic analysis. Finally, the use of administrative databases facilitates a larger study population — including an external control group consisting of all other Ontario hospitals not allocated to an intervention — at lower research operating costs.

### Limitations

While this study proposal highlights the evaluation of a simple, yet novel, approach to improve cardiac medication adherence post-MI, there are methodological limitations. First, the use of administrative databases limits (1) the evaluation of prescription fills rather than swallowing of pills and (2) the assessment of medications and patients not covered by the ODB plan, including aspirin and those <65 years old, respectively. Second, while the interrupted time series analysis can support causal inference, the design is not as robust as an RCT. We do plan to collect appropriate province-wide data throughout this study to inform the design of a future randomized trial. Finally, it is acknowledged that some patients who are classified as nonadherent may have moved away from Ontario, and thus, their prescription claims may be under a different provincial plan for part of the follow-up, leading to potential underestimation of their cardiac medication adherence. The information obtained from this study will help inform the design of a multicenter RCT as an alternative approach to evaluate this proposed intervention.

### Conclusions

In conclusion, the MIPAD study is the first prospective study to evaluate the effects of implementing an institutional policy or standardized discharge cardiac medication prescriptions of maximum duration on long-term medication adherence. The results of this study have the potential to redefine best practices regarding discharge prescribing policy for patients post-MI. Instituting a policy of standardized maximum-duration prescriptions at the time of discharge post-MI is a simple intervention that has the potential to significantly improve long-term medication adherence, thus decreasing cardiac morbidity and mortality. If effective, this low-cost intervention could be easily scaled. Furthermore, since nonadherence is not unique to post-MI patients, this intervention could improve medication adherence in patients with other chronic diseases.

## Appendix

Multimedia Appendix 1 Identification of Cardiac Care Network - Cardiac Registry (CCN-CR) claims for a cardiac catheterization with the primary referral reason being a ST-elevation myocardial infarction (STEMI) or non-STEMI with evidence of coronary artery disease.

## Abbreviations

CAD: coronary artery disease
CCN-CR: Cardiac Care Network - Cardiac Registry
HHS: Hamilton Health Sciences
MACE: major adverse cardiac events
MI: myocardial infarction
MIPAD: Myocardial Infarction Prescription Duration Study
NHS: Niagara Health Services
ODB: Ontario Drug Benefit
OR: odds ratio
PDC: proportion of days covered
RCT: randomized controlled trial
STEMI: ST-elevation myocardial infarction
